### Secondary analysis

For the secondary outcomes, the amount of bleeding during operation and mortality within 30 days will be presented as mean (or median) difference and 95% CI. GEE will be deployed to compare the difference among interventions or clusters. All the analyses will adjust cluster effect, period effect, and interaction among interventions and periods if applicable.

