## Methods and analysis

### Study design

This study is a cluster-randomized crossover, multicenter exploratory trial that is designed to assess the safety and efficacy of multiple intervention measures for preventing VTE among perioperative orthopedic trauma patients. The unit of randomization is the orthopedic wards, and each ward will define a cluster, as the proposed interventions are designed to be implemented in all orthopedic wards rather than in selected individual subjects. The study will be conducted at four hospitals in Shanghai from December 2019 through December 2023, including (1) Shanghai Sixth People’s Hospital, Shanghai Jiao Tong University School of Medicine; (2) Jinshan Branch of Shanghai Sixth People’s Hospital, Shanghai Jiao Tong University School of Medicine; (3) Lingang Compound of Shanghai Sixth People’s Hospital, Shanghai Jiao Tong University School of Medicine; and (4) Shanghai Tenth People’s Hospital, Tongji University. A total of five clusters will be determined in the study, according to the routine amount of orthopedic trauma patients visited in those hospitals.

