### Proposed sample size

We determined the sample size based on the cumulative incidence of VTE. It is estimated that at least 398 orthopedic trauma patients need to be enrolled in each of the five clusters to achieve a power value of 85% to detect an absolute difference of 10% in the cumulative incidence of VTE between the patients with intervention measures and those with control measures (assuming a VTE incidence of 15% according to our retrospective cohort study [5]) at a two-sided alpha level of 0.05. Consequently, approximately 40 patients will be enrolled per intervention measure/control measure per calendar month in each cluster, totaling 1990 patients. The intraclass correlation coefficient (ICC) was calculated based on two levels, 0.228 for patients within the same cluster/time period and 0.15 for patients within the same cluster/different time periods. Due to the lack of data on ICCs related to the current study design and primary outcome, we chose to use a conservative ICC value in our sample size estimation. Moreover, considering a 20% loss of participants, we determine to enroll a total of 2490 patients in the trial, with 498 in each cluster.

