### Data collection

In this study, the primary outcome is the incidence of VTE, which will be measured by trained orthopedists using ultrasound examination (Mindray M8, 8.0–11.0 MHz, China) [17]. Additionally, adverse events following the administration of LWMH and/or IPC will also be recorded and judged by experienced orthopedists, pharmacists, and intensivists, to assess the safety of multiple intervention measures.

The secondary outcomes include the amount of bleeding during operation and mortality within 30 days. Related data will be collected through the hospital information system (HIS) using a standardized case report form (CRF) and recorded using EpiData 4.2. Participants will be followed up from study enrollment to hospital discharge, 30 days after discharge.

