### Data analysis

#### Statistical analysis principles

We will generally perform the analysis using the intention-to-treat (ITT) at the subject level for each outcome. All the participants with a recorded outcome will be included in the analysis according to the intervention group to which they have been randomized. Additionally, we will take the cluster-randomized crossover design effect into consideration. Adjustment for multiple comparisons among interventions will be used. The SAS 9.4 software will be used for all statistical analyses.

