### Subgroup analysis

For the primary outcome, efficacy among interventions will be determined according to the Caprini score and TI score, as well as sociodemographic and clinical groups. To test for interactions, the consistency of intervention effect across the subgroups will be assessed. Bonferroni correction will be used to adjust subgroup analyses for multiple comparisons.

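### The secondary analysis plans GEE comparisons among the five wards, which are not randomised groups, answer no stated hypothesis and have no reliable standard error

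*Protocol article*

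**What the plan says.** The protocol article names two secondary outcomes (Data collection): "The secondary outcomes include the amount of bleeding during operation and mortality within 30 days". For these, the Secondary analysis section states: "GEE will be deployed to compare the difference among interventions or clusters". Its next sentence is: "All the analyses will adjust cluster effect, period effect, and interaction among interventions and periods if applicable". The Primary analysis section uses GEE for VTE with cluster only as something to adjust for, and plans no comparison of clusters.

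On what a cluster is, the Study design section says "The unit of randomization is the orthopedic wards, and each ward will define a cluster" and "A total of five clusters will be determined in the study". Under Interventions, the measures rotate by calendar month within each ward, and the abstract has every cluster running all five.

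Two sentences deal with multiplicity. Statistical analysis principles has "Adjustment for multiple comparisons among interventions will be used". Subgroup analysis has "Bonferroni correction will be used to adjust subgroup analyses for multiple comparisons", in a section that concerns the primary outcome. The section on hypothesis and outcomes contains nothing about differences between wards.

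**The concern.** The randomisation decides which measure a ward uses in which month. It creates no comparable groups of patients across wards. A difference in blood loss or mortality between two wards in four hospitals may reflect case mix, surgeons or local practice, and says nothing about heparin or compression.

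There is also a technical problem. Each side of a ward contrast is a single cluster. The robust variance that usually goes with GEE relies on many independent clusters, and here there are five. Neither multiplicity sentence reaches the ward contrasts.

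At stake is whether p-values or intervals for ward differences in mortality and bleeding, with no controlled error rate, are reported beside the comparisons that the trial was randomised to make.

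**Working it through.** The protocol gives no error rate for ward comparisons, so there is no figure to reproduce. The check asks how often ward contrasts would be significant if the wards did not differ.

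**Inputs from the protocol**
- Five wards (Study design) and two secondary outcomes (Data collection).
- 398 patients per ward before losses, and about 40 per ward-month (Proposed sample size). These are taken as given; nothing here turns on how 398 was derived.
- Ten periods per ward (Fig. 1 caption, described there as hypothetical).

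**Assumptions**
- Wards are compared in pairs.
- Each pair is tested "at a two-sided alpha level of 0.05", which the protocol states only for the sample size.
- The binary outcome has a 3% event rate, an arbitrary value because the protocol gives no mortality rate.

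**Step 1: number of contrasts.** 5 × 4 / 2 = 10 pairs per outcome, so 20 over two outcomes.

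**Step 2: most favourable case, valid individual-level standard errors.** With patient SD 1, the SE of a ward difference is √(2/398) = 0.071. The chance that at least one of ten pairs is significant is the upper tail of the studentized range for five groups at 1.96 × √2 = 2.77, which is 0.286. A simulation of 20,000 trials gave 0.283. Ten independent tests would give 1 − 0.95^10 = 0.40; ward pairs share wards, so the true figure is lower. Bonferroni at 0.05/10 = 0.005 brings it to 0.04.

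**Step 3: GEE with robust standard errors.** The simulation had no ward difference, five wards, ten months, Poisson(40) patients per ward-month, terms for ward, measure and period, independence working correlation, and 200 trials per row. The model-based SE is for one contrast in one simulated trial.

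| Clustering unit | Outcome | Median robust SE | Model-based SE | Single pairs significant | At least one of ten |
|---|---|---|---|---|---|
| Ward | Continuous | 0.004 | 0.071 | 90% | 100% |
| Ward | Continuous, ward-month SD 0.29 | 0.009 | 0.070 | 91% | 100% |
| Ward | Binary, 3% | 0.056 | 0.43 | 79% | 100% |
| Ward-month | Continuous | 0.055 | 0.072 | 14% | 60% |
| Ward-month | Continuous, ward-month SD 0.29 | 0.116 | 0.074 | 13% | 50.5% |
| Ward-month | Binary, 3% | 0.33 | 0.49 | 13% | 57% |

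The ward-month SD of 0.29 corresponds to 0.29² / (1 + 0.29²) = 0.078, the gap between the protocol's two ICCs for VTE (0.228 − 0.15). Monte Carlo error at 0.60 is √(0.6 × 0.4/200) = 0.035.

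**Step 4: why.** When ward is both a model term and the clustering unit, the fitted residuals sum to zero within each ward. Those ward sums are what the robust variance of the ward terms is built from, so it collapses. With equal ward-month sizes it was zero to machine precision.

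With ward-month clustering the robust SE is too small. In the fifth row it is 0.116, against about √(2 × (1/400 + 0.29²/10)) = 0.148, a ratio of 0.78. This fits a model with 18 coefficients on 50 ward-months, for which √(32/50) = 0.80.

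**Step 5: the remaining reading.** If ward enters only through the working correlation, nothing collapses, but the model then has no ward term and no ward contrast to report.

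**The case against.** The strongest reply is that most of this rests on choices the protocol does not make. It names no clustering unit, working correlation, variance estimator or fixed ward term, and an article may leave those to an analysis plan. A difference among wards could be examined with one 4-df test, which has no family of ten. With ordinary valid standard errors the 0.29 is the familiar rate for all pairs of five groups, each pair still at 5%. The Study design section already calls the trial exploratory, and the wording may mean no more than comparing interventions while allowing for clusters.

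Much of this stands, and it rules out some stronger readings that a reader might infer:

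- **That ward differences would be significant almost regardless of the data.** This holds only if ward is both a model term and the clustering unit with robust variance, and wards are tested in pairs. The protocol specifies none of these.
- **That the plan's own ICC makes significance near-certain.** Taking 0.15 as the ward ICC, at least one pair is significant in 0.9996 of simulated trials. That would be detection of real ward differences, not a false-positive rate, and the ICC is given for a sample size based on VTE, not for bleeding or mortality.
- **That comparing wards contradicts adjusting for ward.** One model can estimate measure effects adjusted for ward and ward effects adjusted for measure. The two sentences sit awkwardly together but do not conflict.

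The reply does not rescue the phrase itself. Planning to compare clusters is stated text, not a detail left to another document. A single global test would avoid the ten pairs, but it would still compare five non-randomised units on a question that the trial does not pose.

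**Conclusion.** The point holds as a minor one. The secondary analysis names wards as an object of GEE comparison although they are not randomised groups, no hypothesis concerns them, and the stated multiplicity adjustment does not cover them.

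If wards are compared in pairs at 0.05 with no true difference, the chance of at least one significant pair per outcome runs from about 0.29 to about 1.0, depending on a variance choice that the protocol leaves open. Neither robust GEE version tried held its nominal level: single pairs were significant in 13–14% of tests with ward-month clustering and in 79–91% with ward clustering. These figures assume pairwise testing, ten months of about 40 patients per ward, and the modelling choices listed in the working.

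A reader might go on to infer that the randomised secondary results are compromised. The documents do not support that: the comparisons among the five measures and the primary analysis do not depend on the ward contrasts.

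**What to change.** In the Secondary analysis section, delete the words *or clusters*, so that GEE compares the five measures, with ward and period only as adjustment terms. Report blood loss and 30-day mortality by ward in a descriptive table without p-values.

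Keeping the ward tests and adding Bonferroni is a weaker remedy. It brings the valid-SE case to about 0.04 but does not repair a robust variance that has collapsed or is too small.

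The change is one phrase and costs no data, patients or power. The downside is that ward differences are shown but no longer tested. If the authors only meant to compare interventions while accounting for clusters, the edit makes the text say so.

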### Subgroup analysis

For the primary outcome, efficacy among interventions will be determined according to the Caprini score and TI score, as well as sociodemographic and clinical groups. To test for interactions, the consistency of intervention effect across the subgroups will be assessed. Bonferroni correction will be used to adjust subgroup analyses for multiple comparisons.

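### The subgroup analyses are fixed on Bonferroni, although Holm's step-down procedure rejects at least as much at the same family-wise error rate: a small, cheap improvement

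*Protocol article*

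**What the plan says.** The Subgroup analysis section of the Protocol article plans, for the primary outcome, that "efficacy among interventions will be determined according to the Caprini score and TI score, as well as sociodemographic and clinical groups". It then says: "To test for interactions, the consistency of intervention effect across the subgroups will be assessed". The correction is named outright: "Bonferroni correction will be used to adjust subgroup analyses for multiple comparisons".

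The section gives no divisor, no definition of the family and no power for any interaction test. A separate adjustment for comparisons among interventions is announced under Statistical analysis principles, without a named method. That supports reading the Bonferroni sentence as a correction across subgroup analyses. The significance level, "at a two-sided alpha level of 0.05", is stated under Proposed sample size for the primary comparison only. Study design describes the trial as exploratory.

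**The concern.** The plan commits to a particular multiplicity method, so this is a stated choice and not a detail left for later. Bonferroni tests every hypothesis at α/m. Holm starts at α/m and relaxes the threshold after each rejection, with the same guarantee on the family-wise error. Choosing Bonferroni gives up some power and gains no error control.

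At stake is the chance of detecting a real difference in effect, for example by Caprini or TI score. If such a difference is missed, the effect is more likely to be reported as consistent across subgroups. Neither method changes how the interaction p-values are obtained; both take them as given.

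**Working it through.** **Inputs.** From the document: Bonferroni for subgroup analyses; two-sided α = 0.05, stated for the primary comparison and assumed here as the family-wise level for the subgroup tests. Not in the document, and assumed: the number of tests m (range 2 to 20), independent tests, and unadjusted power of 80% per real interaction (50% as a second case). The plan states no figure on this point, so there is none to reproduce.

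**1. Rejections.** Order the p-values. Holm compares the j-th smallest with α/(m − j + 1) and stops at the first failure. Every such threshold is at least α/m. If k p-values are at or below α/m, the k smallest all pass, so Holm rejects whatever Bonferroni rejects.

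**2. Error rate.** Let m0 hypotheses be truly null. The first true null that Holm rejects is met no later than step m − m0 + 1, where the threshold is at most α/m0. A false rejection therefore needs some true null with p ≤ α/m0. By Boole's inequality the probability of that is at most m0 × α/m0 = α. Independence is not used.

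**3. Bonferroni power.** Power = Φ(θ − z), where z is the two-sided critical value at 0.05/m and θ = 1.960 + 0.842 = 2.802 for 80% unadjusted power.
- m=2: Φ(2.802 − 2.241) = 71.2%
- m=4: Φ(2.802 − 2.498) = 61.9%
- m=10: Φ(2.802 − 2.807) = 49.8%

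Five measures give a joint interaction test with 4 degrees of freedom for a two-level subgroup. A noncentral chi-square version with 4 df gives 71.4%, 62.4% and 50.6%, so the form of the test matters little.

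**4. Holm at m=2, both interactions real (closed form).** A test is rejected if p ≤ 0.025, or if 0.025 < p ≤ 0.05 and the other test has p ≤ 0.025:

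0.7123 + (0.8000 − 0.7123) × 0.7123 = 0.7123 + 0.0625 = 0.7748.

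With only one real, the other test passes 0.025 by chance: 0.7123 + 0.0877 × 0.025 = 0.7145, a gain of 0.2 points.

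**5. Larger m, by simulation.** 200,000 replicates of independent two-sided z-tests; the standard error per test is at most √(0.25/200,000) = 0.11 points. Average power per real interaction, two real, 80% unadjusted power:

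| m | Bonferroni | Holm | Gain (points) |
|---|---|---|---|
| 2 | 71.2% | 77.5% | 6.3 |
| 4 | 62.0% | 64.5% | 2.5 |
| 6 | 56.6% | 58.1% | 1.5 |
| 10 | 49.7% | 50.5% | 0.8 |
| 20 | 41.4% | 41.7% | 0.3 |

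The gain shrinks with m because one rejection only moves the divisor from m to m − 1.

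Other cases:
- One real interaction: 71.35% v 71.57% at m=2, 56.64% v 56.75% at m=6, 49.83% v 49.88% at m=10.
- All six of six real: 56.5% v 68.3%.
- 50% unadjusted power, two real: 39.03% v 43.35% at m=2, 19.86% v 20.10% at m=10.

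Simulated family-wise error stayed below 0.05 for both methods in every case where a true null was present.

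**The case against.** The strongest reply is that Bonferroni is a legitimate, familiar method that contradicts nothing in the article. The subgroup analyses are secondary in an exploratory trial, no power is claimed for them, and the plan reports its outcomes with 95% confidence intervals, for which Bonferroni has simple simultaneous versions and Holm does not. All of this stands, and it is why the point is minor. It does not remove the fact that on rejections Holm is never worse and sometimes better.

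Three stronger readings are tempting and are not supported.

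- **An open-ended family.** From "according to the Caprini score and TI score, as well as sociodemographic and clinical groups" a reader might infer that the two scores share one family with an unlimited list of groups, so that each added group tightens their threshold. The article states neither a divisor nor a family, and does not say that groups may be added freely. Listing the subgroups is commonly left to the full protocol or analysis plan, which is not shown.
- **A large loss caused by Bonferroni.** Under Bonferroni, power falls from 71% at m=2 to 41% at m=20. A reader might charge that to the method, but it comes from the number of tests. Holm falls too, from 77.5% to 41.7% with two real interactions.
- **Formal tests for the two scores only.** Restricting testing in this way would be a design preference, not a correction. Quality assurance and data management lists both scores among the recorded measurements without giving them a subgroup purpose.

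**Conclusion.** The point holds as a minor efficiency improvement. That Holm controls the same family-wise error under any dependence and rejects everything Bonferroni rejects is a mathematical result and needs no assumption about m, the family or the tests.

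The size of the gain does rest on assumptions: independent tests, 80% unadjusted power each and a family-wise level of 0.05. On these, with two real interactions, it is about 6 points of average power at m=2, 2.5 at m=4 and about 1 at m=6 to 10. With one real interaction it is close to nil. It becomes large only if most tested interactions are real. Nothing in the plan is invalid or misstated on this point, and the article does not support a claim that subgroup power is seriously damaged by the choice.

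**What to change.** In the Subgroup analysis section, replace the Bonferroni correction by Holm's step-down procedure for the subgroup tests, at the family-wise level already intended. Add that confidence intervals for subgroup effects are unadjusted 95% intervals and will be labelled so. The groups to be tested need not change.

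The cost is one edited sentence and one added clause; sample size and data collection are not affected. The downside is the loss of simple simultaneous intervals that match the tests, so an interval and its adjusted test may occasionally seem to disagree. The label on the intervals deals with that.

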## Discussion

VTE is a complication that cannot be underestimated after major orthopedic surgery, which is challenging to find and diagnose. Early identification, early assessment, and early prevention can significantly reduce the incidence of VTE. Numerous approaches to prevent VTE have been developed and evaluated. Most guidelines recommend both medical and physical prevention, and we hope to demonstrate how they would affect the incidence among perioperative orthopedic patients.

Our study design has strengths. First, the design of a clustered crossover trial would facilitate the statistical power to detect possible differences among multiple intervention measures. Second, the format of orthopedic wards as randomized clusters will enhance the fidelity of the interventions, which will be performed by same orthopedists. Third, the study will include a larger sample size of orthopedic trauma patients, which will improve the robustness of the findings. However, there is a limitation to this study design. The crossover design might lead to difficulty in the implementation of the trial.

### Trial status

The protocol version number: 001; date: 17 November 2019.

Recruitment began in December 2019 and is expected to complete in December 2023 (Fig. 3).

**Fig. 3 Fig3:**
[figure not shown]
The enrollment, intervention, and assessment schedule for this study

The date of the latest Ethical Approval Extension document is December 21, 2022, with a validity period of 1 year, which is still within the current effective period. If necessary, we will apply for a new extension.

## Data Availability

The datasets generated during and/or analyzed during the current study are not publicly available due to the privacy policy but are available from the corresponding author upon reasonable request.

## Abbreviations

VTE: Venous thromboembolism
LMWH: Low molecular weight heparin
IPC: Intermittent pneumatic compression
ITT: Intention-to-treat
GEE: Generalized estimating equation
HIS: Hospital information system
CRF: Case report form
